The 7-day PAR is a general measure of physical activity, which has been recognized as valid and reliable tool in recent years and is widely used in epidemiological, clinical and behavior change studies. It consists of a semi-structured interview (10-15 minutes) in which participants provide an estimate of the number of hours dedicated to physical or occupational activities requiring at least a moderate effort in the past seven days. The categories collected are moderate, vigorous, and very vigorous physical activity. The amount of time dedicated to each activity is multiplied by the mean metabolic equivalents (METs) of each category: light activity 1.5, moderate 4, vigorous 6, and very vigorous 10. The sum of the products of the hours dedicated to each activity and its estimated mean energy expenditure (MET) provides an estimation of the kilocalories per kilogram used per day (kcal*kg-1 * d-1). The dose of physical exercise will be estimated in METs/hour/week and active persons were considered as those doing at least 30 minutes of moderate activity, five days a week, or at least 20 minutes of vigorous activity, 3 days a week or 450 MET · min · wk^-1 ^[12]. Persons not reaching this level of physical activity were considered sedentary.

Questionnaire hours seated (Marshall): Evaluates the hours that the individual is sitting, in their work, in the displacements and at home, during the week and the weekend [55].

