### Intervention

#### *Common to both groups*

##### 

**Counseling on physical activity** Both groups (control and intervention) will receive counseling on physical activity with a view to favoring compliance with the current recommendations on physical activity in the general population. The intervention has demonstrated its effectiveness in the PEPAF study [14] and in the *Prescribe Vida Saludable* (PSV) program (Osakidetza). Counseling will consist of an individual visit lasting 15 minutes in which an explanation will be given of the health benefits of physical activity, with the recommendation to perform at least 30 minutes of moderate activity 5 days a week, or 20 minutes of vigorous activity three days a week. Counseling will be standardized in both groups, and the subjects will receive an informational brochure (Additional file 1) on the session. The first part (5 min.) will address the recommendations on physical exercise in relation to cardiovascular health. The second part (8 min.) will develop knowledge of the intensity of some specific physical activities such as walking, riding a bicycle, or other activities. The last part (2 min.) will be dedicated to answering questions and doubts. Specific advice will be given to reduce the number of hours spent sitting.

##### 

**Nutritional counseling** Both groups (control and intervention) will receive nutrition counseling aimed at favoring adherence to the MD. This intervention has been shown to be effective in the PREDIMED study [22]. Counseling will consist of an individual visit lasting 15 minutes in which the concepts of the MD will be explained, with insistence upon the importance of complying with each of the recommended points. Counseling will be standardized in both groups, and the subjects will receive an informational brochure (Additional file 1) on the session. The first part (3 min.) will develop the concept of the MD. The second part of the session (10 min.) will focus on each particular recommendation, with brief and clear messages. The last part of the interview (2 min.) will be dedicated to answering questions and doubts.

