### Statistical analysis

The results will be expressed as the mean ± standard deviation for quantitative variables or using the frequency distribution for qualitative variables. Analysis of the results will be made on an intent-to-treat (ITT) basis. Statistical normality will be tested using the Kolmogorov-Smirnov test. Use will be made of the chi-squared test to analyze the association between independent qualitative variables, along with the McNemar test for paired samples. The Student t-test will be used for the comparison of means between two groups, and the paired t-test will be applied to assess changes within one same group. Alternatively, the corresponding nonparametric tests will be used, as required. The relationship between quantitative variables will be analyzed using Pearson’s correlation coefficient or Spearman coefficient in the case of asymmetrically distributed variables. Multivariate linear regression analysis and logistic regression analysis will be used to analyze the variables determining the changes in physical activity and eating habits, and in the arterial stiffness parameters (PWV, AIx and CAVI). In order to analyze the effect of the intervention, comparison will be made of the changes observed in the control group (CG) versus the intervention group (IG), with estimation of the Cohen d statistic, adjusting for the variables that may influence the results. Logistic regression will analyze the odds ratio (OR) for achieving the objectives of diet and exercise compliance. A multilevel analysis will be performed to determine the effect of the different recruitment centers. Gender will be contemplated in the analysis to assess differences between males and females in terms of adherence to the smartphone application, and in the middle- and long-term results. Likewise, an analysis will be made according to the degree of motivation at baseline assessment and adherence to use of the smartphone. The effect of the intervention could be modified by age, gender, cultural and socioeconomic level, body mass index (BMI) and certain disease conditions, as well as by the baseline lifestyles, which will be controlled in the analysis. The contrasting of hypotheses establishes α = 0.05. The IBM-SPSS version 20.0 statistical package will be used throughout.

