## Discussion

The exponential development of smartphone applications in the field of healthcare has not been accompanied by sufficient scientific evidence of the usefulness of such applications in improving the health of the population. As has already been called upon by different organisms, and more specifically by the FDA, it seems necessary to conduct experimental studies similar to those used in pharmacological treatments, in order to obtain sufficient scientific evidence of the possible usefulness of these tools.

The EVIDENT I study obtained evidence of the association between healthy lifestyles - particularly physical activity and diet – and vascular structure and function. Specifically, less physical activity or prolonged sedentarism was associated to greater aging of the vascular system [10,68].

The EVIDENT II study developed a smartphone application that has already been tested in a prior pilot phase designed to assess its reliability in the recording and analysis of diet and physical activity, as well as in relation to the counseling needed to improve these parameters and come closer to the international recommendations referred to the compliance with the Mediterranean diet and physical activity equivalent to at least 10,000 steps a day.

With this project we hope to demonstrate that regular use of this application for at least three months is able to modify certain habits, resulting in eating habits more in line with the Mediterranean diet, which has already demonstrated its benefits in terms of cardiovascular morbidity-mortality [30]. Likewise, we hope to increase the physical activity of the participants and to raise the proportion of individuals considered to be active, as this should imply multiple improvements in health – as has already been demonstrated in different studies [1-3].

Although over the short term it will be difficult to demonstrate the health benefits of the changes in diet and physical activity, over the middle term we hope to demonstrate that the use of this tool can not only improve living habits but also afford benefits in terms of vascular function - improving the parameters that assess arterial stiffness, such as AIx, CAVI and PWV.

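### The 450 MET·min/week route to *active* is not on the scale of the PAR weights, so moderate activity alone qualifies from 112.5 min/week, below the counselled 150 min

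*Protocol article*

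**What the plan says.** All the scoring elements stand in the PAR paragraph of the protocol article's Physical activity section.

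- **Weights.** Time in each category is multiplied by a MET value: "light activity 1.5, moderate 4, vigorous 6, and very vigorous 10".
- **Categories recorded.** "The categories collected are moderate, vigorous, and very vigorous physical activity".
- **Definition of active.** Three routes are joined by *or*: "at least 30 minutes of moderate activity, five days a week", then "or at least 20 minutes of vigorous activity, 3 days a week or 450 MET"·min per week. The text neither limits the third route to mixed activity nor gives it other weights.
- **Everyone else.** "Persons not reaching this level of physical activity were considered sedentary", so the classification is binary.

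Three other places bear on its use. The counseling given to both groups (Intervention, Common to both groups) sets the target as "at least 30 minutes of moderate activity 5 days a week, or 20 minutes of vigorous activity three days a week", with no MET-minute alternative. The Statistical analysis section states: "Logistic regression will analyze the odds ratio (OR) for achieving the objectives of diet and exercise compliance". The Discussion hopes to "raise the proportion of individuals considered to be active".

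**The concern.** A MET-minute threshold means something only together with the weights used to compute MET-minutes. Here the same paragraph gives both, and they do not fit. A participant who does only moderate activity can miss the target on which both arms are counselled and still be classed as active.

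If this classification is the response variable for exercise compliance, the odds ratio would describe a looser standard than the one the intervention promotes. Some participants would also count as already active at baseline who would not do so against the counselled target.

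**Working it through.** **Inputs.** Weights of 4 (moderate), 6 (vigorous) and 10 (very vigorous); time criteria of 30 min × 5 days and 20 min × 3 days; threshold of 450 MET·min/week. All are from the Physical activity section. The counselled target is from the Intervention section.

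**Step 1: can 450 be reproduced?** Formula: minutes × days × weight.

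- Moderate criterion: 30 × 5 × 4 = 600
- Vigorous criterion: 20 × 3 × 6 = 360
- The same time at the very vigorous weight: 20 × 3 × 10 = 600

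None gives 450. Solving for the weight that would: 450 / 150 min = 3 METs for moderate, or 450 / 60 min = 7.5 METs for vigorous. Neither weight appears in the article.

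**Step 2: what the 450 route requires with the stated weights.**

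| Activity done alone | Minutes per week to reach 450 | Time criterion, minutes per week |
|---|---|---|
| Moderate | 450 / 4 = 112.5 | 150 |
| Vigorous | 450 / 6 = 75 | 60 |
| Very vigorous | 450 / 10 = 45 | none stated separately |

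For moderate activity, 112.5 / 150 = 0.75, so the bar is 25% lower. It is equivalent to 22.5 min on five days, and no spread over days is required.

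**Step 3: which routes decide a case?** Let m and v be weekly minutes of moderate and vigorous activity.

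- If m ≥ 150, then 4m + 6v ≥ 600 > 450. Whoever meets the moderate criterion has already met the MET-minute route, so the moderate criterion never changes a classification.
- If v is 60 to 74 and m = 0, the total is 360 to 444, below 450. The vigorous criterion still decides such cases.

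A grid of whole minutes from 0 to 300 for m and v, ignoring the spread over days, agrees. No point qualifies by the moderate criterion alone, 184 qualify by the vigorous criterion alone, and 4,890 by the 450 route alone. These are grid points, not expected participants.

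**Step 4: who is affected?** Among people with no vigorous activity, those from 112.5 to just under 150 min/week of moderate activity are classed as active but miss the counselled target. Some mixed patterns qualify in the same way. The article gives no distribution of PAR minutes, so the share of participants cannot be computed.

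**The case against.** **The routes are alternatives, not equivalents.** The text never says that 450 was derived from 150 minutes at weight 4. The two time criteria already differ (600 and 360), 450 lies between them, and the definition cites a source that is not at hand. A third route intended for mixed activity is plausible. This stands to the extent that 450 cannot be called a miscalculation, and the intended value cannot be settled from the article. It does not rescue the rule as written, which admits purely moderate activity and applies a weight of 4.

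**The 25% shortfall is one-sided.** The counselled target also has a vigorous option worth 360 MET·min, and 450 / 360 = 1.25. This stands: the shortfall holds only for purely moderate activity.

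**The link to the logistic regression is inferred.** The Statistical analysis section does not name the variable behind exercise compliance. The description of the smartphone tool gives another definition of an active individual, 10,000 steps a day. This stands, so the PAR classification is the likely basis and not a stated one. The step figure is the app's target, and only the intervention group receives the app. The PAR definition is not tied to one arm.

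**The main results are untouched.** This stands. The abstract does list the PAR among the instruments for the main endpoints, but the Physical activity section assigns the principal activity endpoint to the accelerometer, with counts/minute as its main outcome. The activity sample size also rests on counts/minute. The continuous PAR dose does not use the cut-off either.

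**Raising the threshold to 600 does not end the redundancy.** This is true: 150 min of moderate activity still gives at least 600. But the two bars for moderate activity would then coincide, so the redundancy would no longer loosen the target in minutes.

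**Conclusion.** The point holds for a secondary binary measure. Within one paragraph the 450 threshold and the moderate weight of 4 are on different scales. For purely moderate activity the effective bar is 112.5 instead of 150 min/week, and the moderate time criterion never decides a case.

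Two assumptions underlie this: the stated weights are used to compute the MET-minutes for this classification, and *or* is applied literally. If moderate activity were weighted 3, 450 would correspond to 150 min and the gap for moderate activity would vanish. At an assumed 3.5, not in the article, the bar would be 450 / 3.5 = 128.6 min.

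A reader might infer that the trial's odds ratio for activity is biased, or that its primary result is at risk. The article supports neither. The rule is the same in both arms, the regression does not name this variable, and the direction and size of any change in the odds ratio are unknown. Relative to the counselled time criteria, the rule can only leave the active proportion unchanged or raise it, at baseline and at follow-up.

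**What to change.** Before the variable is derived:

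1. State in the Statistical analysis section which variable is the exercise objective, and define it by the two time criteria on which both arms are counselled.
2. If a MET-minute route is kept for mixed activity, say so and put it on the same scale as its weights: 600 with moderate = 4, or 450 with moderate = 3 for this classification only. Both correspond to 150 min of moderate activity, but they differ for mixed activity. With vigorous kept at 6, 3m + 6v ≥ 450 is the same as 4m + 8v ≥ 600, which is easier to meet than 4m + 6v ≥ 600 whenever v > 0. The choice must therefore be fixed in advance.
3. Use one version at all visits, and report the present rule (450 with moderate = 4) as a sensitivity analysis.

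The cost is a change to the definition and a re-derivation from PAR minutes already collected. The downside is that the active proportion will be lower or unchanged, and not directly comparable with figures based on 450 at weight 4.

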#### *Nutrition*

Adherence to the Mediterranean diet, principal endpoint of alimentation, will be measured using the validated 14-point Mediterranean Diet Adherence Screener (MEDAS) [56], developed by the PREDIMED study group. The MEDAS is a valid instrument for rapid estimation of adherence to the Mediterranean diet and may be useful in clinical practice. The 14-item screener includes 12 questions on food consumption frequency and two questions on food intake habits considered characteristic of the Spanish Mediterranean diet. Each question will be scored as 0 or 1. One point will be give for using olive oil as the principal source of fat for cooking, preferring white meat over red meat, or for consuming: 1) 4 or more tablespoons (1 tablespoon = 13.5 g) of olive oil/d; 2) 2 or more servings of vegetables/d; 3) 3 or more pieces of fruit/d; 4) < 1 serving of red meat or sausages/d; 5) < 1 serving of animal fat/d; 6) < 1 cup (1 cup = 100 ml) of sugar-sweetened beverages/d; 7) 7 or more servings of red wine/wk; 8) 3 or more servings of pulses/wk; 9) 3 or more servings of fish/wk; 10) fewer than 2 commercial pastries/wk; 11) 3 or more servings of nuts/wk; or 12) 2 or more servings/wk of a dish with a traditional sauce of tomatoes, garlic and onion. The end score will range from 0 to 14. Adequate adherence to the Mediterranean diet will be assumed when the total score is above or equal to 9 points [56].

The dietary habits of participants and information about dairy products were assessed using a semi-quantitative 137-item food-frequency questionnaire previously validated in Spain [57]. The questionnaire was based on the typical portion sizes that were multiplied by the consumption frequency for each food. This estimated frequency corresponds to the previous year at the time of the interview and it is divided into 9 intake frequencies ranging from never to more than 6 servings/day. This will be used to estimate daily energy intake, essential nutrients, vitamins, fiber, antioxidants and other nutrients.

#### *Laboratory determinations*

Venous blood sampling will be performed between 08:00 and 09:00 hours after the individuals fasted and abstained from smoking and the consumption of alcohol and caffeinated beverages for the previous 12 hours. Fasting plasma glucose, creatinine, uric acid, serum total cholesterol, HDL-cholesterol and triglyceride concentrations will be measured using standard enzymatic automated methods. LDL cholesterol will be estimated by the Friedewald equation when the direct parameter will be not available. Glycated haemoglobin will be measured with an immune-turbidimetric assay. High sensitive C-reactive protein levels and fibrinogen concentrations will be determined by immunoturbidimetric assay. Blood samples will be collected in the respective health centers, and all will be analyzed at the hospital of the city participating in external quality assurance programs of the Spanish Society of Clinical Chemistry and Molecular Pathology.

#### *Anthropometric measurements*

Body weight will be determined on two occasions using a homologated electronic scale (Seca 770; Medical scale and measurement systems, Birmingham, United Kingdom) following due calibration (precision ± 0.1 kg), with the patient wearing light clothing and shoeless. These readings will be rounded to 100 g. Height in turn will be measured with a portable system (Seca 222; Medical scale and measurement systems, Birmingham, United Kingdom), recording the average of two readings, and with the patient shoeless in the standing position. The values will be rounded to the closest centimeter. Body mass index (BMI) will be calculated as weight (kg) divided by height squared (m^2^). A value of > 30 kg/m^2^ will be taken to define obesity. Waist circumference will be measured using a flexible graduated measuring tape with the patient in the standing position without clothing. The upper border of the iliac crests will be located, and the tape will be wrapped around above this point, parallel to the floor, ensuring that it will be adjusted without compressing the skin. Adiposity indices, waist-height and waist-hip, will also be calculated.

#### *Office or clinical blood pressure*

Office blood pressure measurement will involve three measurements of systolic blood pressure (SBP) and diastolic blood pressure (DBP), using the average of the last two, with a validated OMRON model M10-IT sphygmomanometer (Omron Health Care, Kyoto, Japan), by following the recommendations of the European Society of Hypertension [58]. Pulse pressure will be estimated with the mean values of the second and third measurements.

#### *Central blood pressure and radial augmentation index*

Central blood pressure (CBP) and radial augmentation index (rAIx) will be measured with Pulse Wave Application Software (B-pro (A-Pulse)) (Health STATS International) using tonometry to capture the radial pulse and by an equation to estimate central blood pressure (CASP). This device has been validated in asian hypertensives and healthy caucasians [59,60]. rAIx is a measurement taken directly from the late systolic shoulder of the peripheral arterial waveform, and is defined as the ratio of the difference between the 2nd peak and diastolic pressure to the difference between the 1st peak and diastolic pressure [61], it is age-dependent and could be a useful index of vascular aging [62]. rAIx will be calculated as follows: (Second peak systolic blood pressure [SBP2] - diastolic blood pressure [DBP])/(first peak SBP - DBP) × 100 (%) and it will be adjusted for heart rate at 75 bpm and it will be reported as rAIx75. Specific aspects regarding the validity and reliability of the measurement of central blood pressure and augmentation index have been reported elsewhere [60]. In brief, the intra-observer reliability was evaluated in 20 subjects by using the intraclass correlation coefficient (ICC), that showed values of r = 0.971 (95% CI: 0.923 to 0.989) for CASP and 0.952 (95% CI: 0.871 to 0.982) for rAIx. According to the Bland-Altman analysis, the mean difference for intraobserver agreement (95% limits of agreement) were -0.056 (-9.41 to 9.30) for CASP and 2.50 (-14.43 and 19.46) for rAIx. In 104 subjects we examined the agreement of measurements with SphygmoCor and found an ICC for CASP r = 0.972 (95%CI 0.959 to 0.981) and for rAIx r = 0.599 (95% CI: 0.409 to 0.728). In Bland–Altman analysis the mean difference for intraobserver agreement (95% limits of agreement) were 1.47 (0.47 to 2.47) in CASP and 5.85 (1.75 to 9.96) in rAIx.

#### *Assessment of vascular structure by carotid intima media thickness (IMT)*

Carotid ultrasound to assess C-IMT will be performed by two investigators trained for this purpose before starting the study. A Sonosite Micromax ultrasound device paired with a 5–10 MHz multi-frequency high-resolution linear transducer with Sonocal software will be used for performing automatic measurements of carotid IMT in order to optimize reproducibility. Measurements will be made of the common carotid after the examination of a 10 mm longitudinal section at a distance of 1 cm from the bifurcation, performing measurements in the proximal and in the distal wall in the lateral, anterior and posterior projections, following an axis perpendicular to the artery to discriminate two lines, one for the intima-blood interface and the other for the media-adventitious interface. A total of 6 measurements will be obtained of the right carotid and other 6 of the left carotid, using average values (average carotid IMT) and maximum values (maximum carotid IMT) automatically calculated by the software [63]. The measurements will be obtained with the subject lying down, with the head extended and slightly turned opposite to the examined carotid artery. The reliability was evaluated before the study began using the intraclass correlation coefficient, which showed values of 0.974 (95% CI: 0.935 to 0.990) for intra-observer agreement on repeated measurements in 20 subjects, and 0.897 (95% CI:0.740 to 0.959) for inter-observer agreement. According to the Bland-Altman analysis, the mean difference for intraobserver agreement (95% limits of agreement) was 0.022 (95% CI: -0.053 to 0.098) and intra-observer agreement was 0.012 (95% CI: -0.034 to 0.059). The average IMT will be considered abnormal if it measured > 0.90 mm, or if there will be atherosclerotic plaques with a diameter of 1.5 mm or a focal increase of 0.5 mm or 50% of the adjacent IMT [64].

